### Clinical Outcome Measures: Primary Outcome

Clinical outcomes will be measured via a digital survey administered at baseline, T2, and T3. The components of the survey and outcome measures are detailed next.

#### Subjective Burden

The primary clinical outcome (ie, caregiver burden) will be measured through the survey using the Zarit Burden Interview [35. Studies have demonstrated a direct association between the caregiver burden and the quality of life for family caregivers [19]. As family caregivers’ appraisal of their ability to cope with their family members’ health condition is a direct predictor of their burden [14], and COMPANION aims to provide the required education and information for fcSCI so that they perceive and experience less challenges in providing care, we have selected fcSCI’s subjective burden as our primary clinical outcome. The short 12-item version of the Zarit Burden Interview will be used to assess the subjective burden [35]. The fcSCI are asked to use a 5-point scale (from 0=never to 4=nearly always) to evaluate how often they experience certain feelings. Total scores can range from a minimum of 0 to a maximum of 48. A total score ranging between 0 and 10 indicates no-to-mild burden, 10-20 indicates a mild-to-moderate burden, and >20 indicates a high burden. This measure has been considered as valid and reliable (Cronbach α=.78) among fcSCI [36].

### Clinical Outcome Measures: Secondary Outcomes

The survey administered at baseline will collect information on participants’ age, sex, gender, social support, annual household income, living situation, and chronic health. The fcSCI will be asked to answer similar questions for individuals with SCI. In addition to demographic information, several secondary outcomes measures will be administered at multiple timepoints. The components of the secondary outcomes measures and their timepoints are detailed next.

#### Objective Burden

The survey will be used to administer several secondary clinical outcome measures. The first secondary outcome will be measured using the 38-item Dutch Objective Burden Inventory assessing fcSCI’s objective burden [37]. Each questionnaire item lists a specific caregiving activity that corresponds to 1 of the following 4 domains: personal care (eg, helping with eating and drinking), practical support (eg, buying groceries), motivational support (eg, motivating to quit or reduce smoking), and emotional support (eg, showing understanding). The fcSCI are asked to rate their perceived burden for each task over the past 3 months using a 3-point scale (1=not at all burdensome, 2=somewhat burdensome, 3=very burdensome). Total scores are calculated as the average of all individual answer scores, ranging from 1 to 3. A higher total score indicates a higher objective burden. Testing of the measure has affirmed adequate validity and reliability among Dutch and Canadian caregivers [38,39].

#### Distress

The second secondary outcome will be measured using a short version of the Depression, Anxiety and Stress Scale (DASS) assessing distress [40]. A short version of the complete 42-item DASS, the DASS-21 contains 21 items assessing depression, anxiety, and stress on 3 separate subscales comprising 7 items each. Participants will report the intensity of their symptoms over the past week using a 4-point Likert scale (from 0=never to 3=always). Separate total scores ranging from a minimum of 0 to a maximum of 42 will be calculated for each subscale. Severity levels for depression, anxiety, and stress can be interpreted based on recommended cutoff scores, with higher scores indicating more distress. Cutoff scores for the Depression subscale distinguish responses as normal (0-9), mild (10-13), moderate (14-20), severe (21-27), and extremely severe (≥28). Testing of the DASS-21 among family caregivers has shown adequate reliability (α coefficient=.97) [41].

#### Relationship Quality Satisfaction

The third secondary outcome will be measured using the Dyadic Adjustment Scale (DAS-32) [42]. The DAS-32 consists of 32 items measuring the level of relationship quality satisfaction among dyads. Items in the DAS-32 correspond to 4 dimensions, or subscales, for measuring relationship quality: dyadic consensus (consensus on matters of importance to marital functioning), dyadic satisfaction, dyadic cohesion (closeness experienced by the couple), and affective expression (demonstrations of affection and sex relations). Each item of the questionnaire corresponds to 1 of the 4 subscales, which consist of varying response scales, including ordinal, Likert, and dichotomous scales. Scores for each subscale are calculated and added together to produce a total score ranging from 0 to 151, with a higher total score indicating less distress and high adjustment. Psychometric testing of the measure has demonstrated good reliability for each subscale (α=.85 for dyadic consensus, .67 for dyadic cohesion, .76 for affective expression, and .82 for dyadic satisfaction) in the general population [42].

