## Introduction

### Background

Approximately 360,000 individuals have spinal cord injury (SCI) in the United States [1] and a further 86,000 in Canada [2]. SCI causes substantial disruption in the patient’s life habits, routines, and level of independence. In many cases, individuals with SCI need considerable human assistance to perform any activities that exceed their motor and sensory capability [3]. Family caregivers (defined as “any relative, partner, friend or neighbor who has a significant personal relationship with, and provides a broad range of assistance for, an older person or an adult with a chronic or disabling condition” [4]) of individuals with SCI (fcSCI) often provide the majority of physical care to their family members with SCI [5]. Furthermore, individuals with SCI may experience higher levels of depression and anxiety and lower levels of life satisfaction than the general population [6]; therefore, fcSCI may also provide emotional support, alongside physical support. Providing physical and emotional care and support can have a substantial impact on fcSCI’s physical and psychological well-being [5]. Many fcSCI report physical, emotional, and financial challenges associated with their caregiving roles and tend to neglect their own mental and physical health [7-9]. Over time, these experiences put fcSCI at high risk of burnout from an increased caregiver burden, which is associated with decreased well-being [5,8].

Caregiver burden is defined as “the extent to which caregivers perceive that caregiving has had an adverse effect on their emotional, social, financial, physical or spiritual functioning” [10]. Previous research indicates that 40%-46% of fcSCI report moderate-to-severe levels of caregiver burden due to the long-term nature of the injury and the caregiver role [10]. The burden associated with caregiving also influences fcSCI’s ability to respond to the needs of individuals with SCI, and the long-term impact of caregiving demands on fcSCI may result in decreased support and quality of care for individuals with SCI. Hence, attending to risk factors and interventions that target the well-being of fcSCI is crucial.

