### Sample Size and Inclusion and Exclusion Criteria

Suggested sample sizes for a feasibility RCT range from 12 to 30 per experimental group [28,29]. We aim to recruit at least 20 participants per group. Inclusion criteria for participants are, at the time of recruitment, as follows:

Family caregiver of an adult individual with SCI (similar to previous studies of this population [30,31]; in this study,family caregiveris defined as an individual who is primarily responsible for providing immediate informal daily care for a relative with SCI).Age >18 years.Living with the individual with SCI in the community.Living in North America.SCI of the patient has not happened within the previous 6 months.

Those fcSCI who had major medical and physical conditions that require routine visits to medical doctors (eg, cancer) will be excluded from the study, in addition to fcSCI providing care to individuals with SCI who are still patients in a rehabilitation facility.

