### Data Analysis

#### Statistical Analysis

All data analysis will be conducted by the research team independently from the study sponsor. Descriptive analysis will be used to describe our sample and consider clinical outcomes and study feasibility. The most current versions of R statistical software (R Foundation for Statistical Computing) [58] and IBM SPSS software [59] will be used. The 1-sample Kolmogorov-Smirnov test will be performed to evaluate data distribution. Demographic and outcome variables will be summarized by groups using means (SDs), frequencies, and proportions. Similar to previous feasibility studies [60], the means (SDs) calculated in the feasibility RCT will be used to estimate the effect size and the variance necessary for the full RCT. Focuses of the analysis will include investigating differences in primary and secondary effectiveness outcomes for the intervention and control groups at each timepoint. We will include an interaction between time and group for all models to account for the possibility of effect modification by time. Estimated marginal means will be used to conduct post hoc analyses, and pairwise comparisons of estimated marginal means will be conducted to examine specific differences between groups at each timepoint. Participant IDs will be used as a random effect. Multiple imputations will be used to deal with missing data. Furthermore, descriptive statistics will be used to assess participants’ online usage data of the eHealth program (eg, the amount of time participants spent accessing the modules) to evaluate feasibility indicators (dose level response, treatment adherence) related to resource and treatment issues [61].

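### The DAS-32 total is a couples' measure, but eligibility is not limited to partners and the plan does not restrict the scale to them, so the total has no valid meaning for non-partner caregivers

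*Protocol article*

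**What the plan says.** All references are to the protocol article.

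- **Instrument (Relationship Quality Satisfaction).** The DAS-32 is the third secondary outcome. Two of its four subscales are described as "dyadic cohesion (closeness experienced by the couple), and affective expression (demonstrations of affection and sex relations". The other two are consensus, which is tied to marriage, and satisfaction, which is named without further description. On scoring: "Scores for each subscale are calculated and added together to produce a total score ranging from 0 to 151". Reliability is cited "in the general population [42".
- **Eligibility (Sample Size and Inclusion and Exclusion Criteria).** A family caregiver is "an individual who is primarily responsible for providing immediate informal daily care for a relative with SCI". The only other criterion that bears on the relationship is living with that person.
- **Administration (Study Timeline).** Participants answer the primary and secondary measures, relationship quality included, from baseline to T3. No subgroup is named.
- **Missing data (Statistical Analysis).** "Multiple imputations will be used to deal with missing data".
- **Recruitment (Recruitment; Discussion, Summary).** One route is a wives' and girlfriends' group of about 6000 members. The others are former patients and research participants, who are asked to pass the invitation to their family caregivers, and social media advertisements.

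**The concern.** The instrument and the eligible population do not match. A mother caring for an adult son, or a sister caring for a brother, meets the criteria but has no marital functioning or sexual relationship with that person to report. Because the total adds all four subscales, content that does not apply in one of them spoils the sum.

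Two things follow. The DAS-32 group comparison would mix couples' adjustment with scores that measure something else, and would depend in part on how many non-partners fall in each arm. The contaminated mean and SD would also carry forward, because the article intends to use this trial's means and SDs to estimate effect size and variance for the full RCT.

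**Working it through.** **1. Text set side by side.**

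| Question | Where | Answer |
|---|---|---|
| What does the scale cover? | Relationship Quality Satisfaction | Marital matters, the couple, sexual relations; one sum of four subscales |
| Who is eligible? | Inclusion criteria | Any co-resident primary carer of a relative with SCI |
| Who completes it? | Study Timeline | Participants generally, baseline to T3 |
| Is it limited to partners? | Nowhere | No |
| Are limits stated for other scales? | Usability | Yes: the SUS is for the intervention group |
| Is a validation gap acknowledged for other scales? | Health-Related Quality of Life | Yes: the VR-12 is said not to be validated in family caregivers |

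The article states a restriction for one scale and a validation caveat for another. For the DAS-32 it gives neither.

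**2. What happens to a non-partner's total.**
- Items left blank and treated as missing: imputation supplies a value for a quantity that is undefined rather than unobserved.
- Items answered because the survey requires it: a response chosen for want of a better one enters the sum, and a low one reads as poor adjustment.

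In neither case is the total a valid measure of relationship quality.

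**3. Scale.** The planned sample reproduces: 20 per group × 2 = 40, as in Table 1. Results reports 54 enrolled. The non-partner share *s* is not given, so it is assumed. With *N* participants, the non-partner count is *k* = *N* × *s*, rounded. A partner-only analysis widens the standard error by √(*N*/(*N* − *k*)), if the SD is unchanged.

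| *N* | *s* (assumed) | *k* | Partners left | SE factor |
|---|---|---|---|---|
| 40 | 10% | 4 | 36 | √(40/36) = 1.05 |
| 40 | 30% | 12 | 28 | √(40/28) = 1.20 |
| 40 | 50% | 20 | 20 | √(40/20) = 1.41 |
| 54 | 10% | 5 | 49 | √(54/49) = 1.05 |
| 54 | 30% | 16 | 38 | √(54/38) = 1.19 |
| 54 | 50% | 27 | 27 | √(54/27) = 1.41 |

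**4. Is the case likely to arise?** If participants are independent draws with *s* = 10%, the chance of at least one non-partner is 1 − 0.9^40 = 98.5% for *N* = 40 and 1 − 0.9^54 = 99.7% for *N* = 54.

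**5. Imbalance between arms.** With *n* per arm and the arms treated as independent binomials, the SD of the difference in non-partner counts is √(2*n s*(1 − *s*)). For *n* = 20 and *s* = 10% this is √3.6 = 1.9. For *n* = 27 (54 split equally) and *s* = 40% it is √12.96 = 3.6. A chance difference of two to four is therefore about one SD across this assumed range.

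**The case against.** Several points on the other side stand and limit the finding.

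- **The sample may be mostly partners.** The wives' and girlfriends' group is the only recruitment route given a size, and the Discussion expects a largely female sample because of it. The non-partner share could be at or below the bottom of the assumed range. The other routes remain open to parents, siblings and adult children, so it cannot be taken as zero.
- **Imputation of these items is not stated.** A reader might infer that the plan will invent marital and sexual answers for non-partners. The article has one general sentence on multiple imputation. It does not say at what level imputation is done or that items that do not apply count as missing, and such detail commonly sits in an analysis plan. The consequence is conditional.
- **Not every item need fail.** A reader might infer that non-partners cannot answer any of the scale. The article gives subscale descriptions only, and some satisfaction or cohesion items may be answerable. The failure is surest for affective expression and marital consensus, and therefore for the total.
- **Friends and neighbors are not shown to be eligible.** The Background definition, "any relative, partner, friend or neighbor who has a significant personal relationship with" the care recipient, is general. The inclusion criteria set the operative one, which refers to a relative.
- **Harm to questionnaire completion** is possible, but nothing in the article demonstrates it.
- **Limited reach.** The DAS-32 is not among the feasibility indicators in Table 1, which drive the success or revise decisions.

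None of this removes the conflict between the scale as described and the caregivers admitted.

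**Conclusion.** The point holds in a limited form. As written, the plan sums a couples' scale for caregivers who need not be partners, and for those who are not, the DAS-32 total has no valid meaning. Whether the damage comes through imputation or through forced answers depends on survey and coding rules that the article does not give.

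The size cannot be fixed from the document. At assumed non-partner shares of 10% to 50%, 4 to 20 of 40, or 5 to 27 of 54, would have no valid total. The true figure may lie at the low end or below it. One secondary outcome of a feasibility trial is affected, and no Table 1 criterion is. It should be corrected before analysis, but it does not threaten the trial's main purpose.

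**What to change.** 1. **Establish relationship type.** Relationship to the person with SCI is not among the baseline items named under Clinical Outcome Measures: Secondary Outcomes. Confirm that it was recorded, or recover it from screening records or from participants, as it stood at enrolment.
2. **Restrict the analysis.** Analyse the DAS-32 total only in spousal or partner caregivers. Relationship at enrolment precedes randomization, so the restriction keeps a randomized comparison.
3. **Code and impute correctly.** Set the total to not applicable in all others, and exclude it from the imputation.
4. **Report the denominator.** Give the number of partner caregivers per arm beside the result and beside any SD carried into the full trial's planning.
5. **Definitive RCT.** Restrict the scale to partners by branching in the survey. Results gives data collection as completed in April 2025, so administration in this trial can no longer change.

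If relationship type is on file, the cost is a filter in the analysis code. If not, it has to be retrieved first; where that fails, the partner-only analysis is not possible and the total should be reported with that limitation. The statistical price is a smaller n for one secondary outcome: a standard error wider by about 5% to 41% over the assumed shares.

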#### Health-Related Quality of Life

The fourth secondary outcome will be measured using the Veterans RAND 12-item Health Survey (VR-12) assessing fcSCI’s health-related quality of life [43]. The VR-12 includes 12 questions corresponding to 8 domains: general health perceptions, physical functioning, role limitations due to physical problems, role limitations due to emotional problems, social functioning, bodily pain, vitality, and mental health [44]. The 8 domains can be summarized into separate physical and mental component scores. The VR-12 scoring algorithm is used to score physical and mental components based on weights derived from a 1990 American population sample standard, resulting in variable minimum and maximum score values [45]. Higher physical and mental components scores indicate better health. Two further questions (ie, 14 in total), which do not contribute to the component summaries, ask about physical health and emotional problems compared to 1 year ago. Health state values (also known as utility scores), reflecting the preferences of the Canadian population, can also be generated from VR-12 data [46]. Though validation of the VR-12 has not been conducted in family caregiver populations, the VR-12 has demonstrated adequate convergent validity in other populations [47].

#### Competence

The fifth secondary outcome will be measured using the Caregiving Competence Scale (CCS) [48]. The CCS is used to measure a caregiver’s self-assessment of the adequacy of their performance in their role. The 4-item questionnaire scores responses using two 4-point scales, with response options ranging from 1=“not at all” to 4=“very much” in the first scale and from 1=“not at all” to 4=“very” in the second scale [48]. Score values range from 0 to 12, with higher scores indicating higher caregiving competence. The CCS has demonstrated adequate internal consistency (Cronbach α=.78-.82) in family caregiver research [49,50].

#### Usability

The sixth secondary outcome will be measured using the System Usability Scale (SUS) to capture the opinion of participants regarding the usability of COMPANION. Originally created by Brooke [51], the SUS consists of a 10-item questionnaire using a 5-point scale, where options range from strongly agree to strongly disagree. Raw scores range from 0 to 40 and are algorithmically converted into meaningful SUS scores ranging from 0 to 100. Higher scores indicate higher perceived usability of the program. Participants in the intervention group will complete this measure at T2 and T3.

#### Caregiver Costs

The final secondary outcome will be measured using the Caregiver Indirect and Informal Care Cost Assessment Questionnaire (CIIQ) to capture information estimating informal care costs [52]. The fcSCI will be asked to provide responses for 13 items with information including, but not limited to, work status, time missed at work, productivity, and physical and emotional caregiving duties. Calculations will be conducted using responses to items on the CIIQ to estimate fcSCI indirect and informal care costs. Total scores can range from as low as 0 to any maximum number and report cost in dollars. Higher scores indicate a greater financial impact due to informal care costs. The CIIQ will be coupled with a bespoke item asking about additional money the fcSCI spend on themselves. To minimize concerns about recall, a 1-week recall period will be used for the CIIQ and a 3-month recall period will be used for the bespoke item.

### Qualitative Interviews

When the feasibility RCT is complete, semistructured interviews (~45-60 minutes) will be used to explore fcSCI’s experiences in the intervention group with COMPANION. The option to take part in the semistructured interviews will be available to participants in the intervention group as soon as they complete T3 survey data collection. An interview guide has been created to capture multiple aspects of fcSCI’s experiences using COMPANION. As a complimentary method to assess usability, the interviews will also be used in combination with the SUS [51] and feasibility indicators to evaluate the usability of COMPANION. Participants will be asked to share their perspective on the advantages and disadvantages of COMPANION. A directed content analysis approach will be used to form initial coding categories from existing evidence and study hypotheses [53].

To promote the credibility and trustworthiness of qualitative data, we will use several methods. Field notes will be used as a self-reflective tool. Member checking will be used; that is, participants will be invited at the end of each interview to review the preliminary findings and provide feedback to determine how well they resonate with them. Multiple investigators with diverse backgrounds will be involved in collaborative theme analysis and data coding as a form of triangulation [54]. Interview results will be integrated with the quantitative results to provide a more in-depth assessment of benefits and user acceptability [55]. Peer debriefing will be used to further support triangulation. To ensure transferability of the qualitative data in our reports, we will follow the Consolidated Criteria for Reporting Qualitative Research (COREQ) report guidelines [56]. Specifically, we will provide detailed information about the setting, participants, and interviewers’ and research team’s backgrounds. We will also provide a detailed description of the data collection procedure, analyses of the qualitative data, and our procedure for developing codes and themes to ensure dependability of our method. Furthermore, we followed the CONSORT (Consolidated Standards of Reporting Trials) eHealth Form (see Multimedia Appendix 2) [57].

